#### Reporting of adverse events

Serious adverse events (deaths) after initiation of the study intervention are recorded and presented to the DSMB within 24 hours of the event. The report includes a detailed clinical history, the study intervention and management given until the outcome. We contacted over the phone for study participants who were referred.

### Operational definition

#### Severe acute malnutrition

A child with a <−3 Z-score of weight for height/length of the median value of the WHO standard or MUAC<115 mm (for children >6 months of age)/visible wasting (for children <6 months of age), or presence of nutritional oedema.

#### Severe underweight

A child with a <−3 Z-score of weight for age of the median value of the WHO standard.

#### Sepsis

Presence of infection/inflammation plus hyperthermia or hypothermia (temperature >38.5°C or<35.0°C, respectively) plus tachycardia (HR: infant >160/min, 1–5 years >140/min) or abnormal WCC (>12×10^9^ ⁄ L or, <4×10^9^ ⁄ L or, band and neutrophil ratio ≥0.1).

#### Severe sepsis

Severe sepsis is defined as the presence of sepsis plus organ dysfunction or tissue hypoperfusion (poor peripheral perfusion (hypotension and/or absent peripheral pulses and/or delayed capillary refilling time (CRT) in the absence of dehydration or after correction of dehydration)).

#### Fluid refractory shock or septic shock

Shock is defined as hypotension (MAP<50 mm Hg) and or reduced urine output <1 mL/kg/hour despite fluid resuscitation.^22^ This 50 mm Hg cut-off was fixed on the basis of our local evidence from the same population.^22^ A child in septic shock usually has a cold periphery, delayed CRT, low volume or absent pulse.

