Children with fluid refractory shock are randomised to blood transfusion, dopamine or epinephrine therapy. Children in the dopamine arm (treatment category A) receive dopamine, 8 μg/kg/min (increasing the dose after 15 min to 12 μg/kg/min to a maximum of 15 μg/kg/min, up to the achievement of goal). Children in the epinephrine arm (treatment category B) receive epinephrine, 0.1 μg/kg/min (increasing the dose after 15 min to 0.2 μg/kg/min to a maximum of 0.3 μg/kg/min, up to the achievement of goal). We are using peripheral lines to give dopamine or epinephrine. Drugs are prepared as intravenous infusion and instilled by an infusion/syringe pump. Children in the blood transfusion arm (treatment category C) receive a transfusion of whole human blood at a dose of 10 mL/kg over 3 hours (figure 1). To arrange blood within the time frame, we have an institutional volunteer donor list, two medical technologists dedicatedly work for this study, and we are also excluding children having negative blood groups. Even after that, If blood could not be arranged within 1 hour after the event of fluid refractory shock, we will start rescue therapy considering the event as treatment failure. In addition to the study interventions, broad-spectrum antibiotic therapy, oxygen therapy and frequent monitoring, all children receive intravenous maintenance fluids with half-strength normal saline and 5% dextrose @ of 3 mL per kg per hour during the arrangement of blood transfusion and intervention with inotropes. Along with maintenance fluid, we add intravenous fluid if diarrhoea continues or a child develops dehydration. Intravenous fluid maintenance is continued for 6 hours after the achievement of a goal and is further continued if the goal is not achieved. Our goal is to achieve MAP>50 mm Hg and/or urine output ≥1 mL/kg per hour. After randomisation, we monitor children at every 15 min interval during the intervention to assess mental status by using AVPU, an acronym from ‘alert, verbal, pain, unresponsive’, capillary refill time, rate and volume of the radial pulse, cold/warm extremities, urine output, blood pressure, respiratory rate, peripheral capillary O_2_ saturation and features of heart failure. We measure BP manually using the standard cuff. To minimise the use of a catheter, we apply a paediatric urine collector bag and measure the urine output. However, for a female child, it is difficult to measure. We are considering an indwelling catheter if required. Mechanical ventilation is provided if the child did not respond to bubble CPAP (if SpO2<85% at least after an hour of bubble CPAP oxygen therapy) or had a respiratory failure (pH<7.2 and Partial pressure of carbon dioxide (PCO_2_)>60 mm Hg in ABG analysis or Oxygen saturation to fraction of inspired oxygen ratio (SpO_2_/FiO_2_)<265). Children who develop complications such as acute abdomen not responding to conservative management or acute renal insufficiency requiring dialysis are referred to a suitable higher facility for proper management. At the achievement of the goal, we continue the dose of dopamine or epinephrine for 6 hours. We follow up with the child every 30 min to 1-hour interval. Thereafter, we reduce the dose in a stepwise manner similar to how we increased the dose. If the child becomes hypotensive again, we reintroduce the previous dose and follow the same procedure for further iteration.

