
### Rescue therapy

The failure of any intervention is declared as a treatment failure. Then for children in the dopamine and blood transfusion arm, we start epinephrine as rescue therapy in a stepwise manner starting from 0.1 μg/kg/min and increasing every 15 min by 0.1 μg/kg/min up to restoration of the desired goal (MAP>50 mm Hg or urine output >1 mL/kg/hour) and the highest dose is 0.5 μg/kg/min (or consultant discretion) For children in the epinephrine arm, the dose is increased every 15 min from 0.3 μg/kg/min (the highest proposed intervention dose) to a max of 0.5 μg/kg/min. On achieving the goal, we continue the same dose for 4–6 hours and then we de-escalate in a stepwise manner.

If the goal is not achieved with injection of epinephrine then injection of norepinephrine is [contact] μg/kg/min and we increase the dose every 15 min by 0.1 μg/kg up to restoration of the desired goal (MAP>50 mm Hg or urine output >1 mL/kg/hour) and the highest dose is 0.5 μg/kg/min. On achieving the goal, we continue the same dose for 6 hours and then will de-escalate in a stepwise manner. For those patients whose MAP is not restored with inotropes, injection hydrocortisone @ 2 mg/kg every 6 hours is added.^19^ During rescue therapy, for doses and selection of any inotrope(s), we are following the recommendation from the Paediatric intensive care unit (PICU) consultant as all cases are not the same.

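### For a child with only one of low MAP and low urine output, the printed shock, goal and failure rules conflict, and MAP-only recovery time is zero or undefined for a child enrolled on urine output alone

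*Protocol article*

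**What the plan says.** All of this is in the protocol article.

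- **Entry** (Operational definition, Fluid refractory shock or septic shock): "Shock is defined as hypotension (MAP<50 mm Hg) and or reduced urine output <1 mL/kg/hour despite fluid resuscitation".
- **Goal during the intervention** (Study intervention and procedure): "Our goal is to achieve MAP>50 mm Hg and/or urine output ≥1 mL/kg per hour". Reaching the goal ends dose escalation. The dose is then held for 6 hours and stepped down.
- **Goal during rescue** (Rescue therapy): "up to restoration of the desired goal (MAP>50 mm Hg or urine output >1 mL/kg/hour".
- **Failure** (Operational definition, Treatment failure): two items, MAP below 50 and urine output below 1 mL/kg/hour, judged when the intervention ends. No *and* or *or* joins them.
- **Separate failure route for blood** (Study intervention and procedure): if blood is not arranged within 1 hour, "we will start rescue therapy considering the event as treatment failure".
- **Consequence of failure** (Rescue therapy): "The failure of any intervention is declared as a treatment failure", after which rescue treatment begins.
- **Recovery time** (Operational definition, and Collection of baseline information): time from the start of the intervention until MAP is restored. Urine output plays no part.
- **Use** (Outcome measures): the treatment failure rate and time to recovery are secondary outcomes. The primary outcome is case fatality at 28±3 days.

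**The concern.** An entry rule that needs one abnormal component and a goal that needs one normal component overlap. A child with MAP 45 and urine output 1.5, or MAP 60 and urine output 0.5, meets both before any study drug is given. At the end of the intervention the same unchanged child is a failure if either failure item suffices, and is not a failure if both are required.

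Two secondary outcomes are at stake. The trial is not masked, so any ambiguity is settled by staff who know the allocation. For recovery time, a child enrolled on urine output alone has no MAP deficit to correct. Zeros or gaps would then enter an arm according to its case mix and not according to its treatment.

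**Working it through.** The plan gives no figure to reproduce here, so the check sets the rules side by side.

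**Step 1. Apply each rule to the four possible states.** Low means MAP<50 or urine output <1. Inputs are the definitions listed above.

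| MAP | Urine output | In shock (entry) | At goal (either suffices) | Failure, any-of | Failure, all-of |
|---|---|---|---|---|---|
| low | low | yes | no | yes | yes |
| low | normal | yes | yes | yes | no |
| normal | low | yes | yes | yes | no |
| normal | normal | no | yes | no | no |

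The conflict lies in the two middle rows, where exactly one component is abnormal.

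**Step 2. Keep the entry rule as printed (*or*) and try each reading of goal and failure.**

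- Goal *or*, failure *or*: a child is in shock and at goal, and at goal and a failure.
- Goal *or*, failure *and*: a child is in shock and at goal, and still in shock but not a failure.
- Goal *and*, failure *and*: a child is short of the goal but not a failure, and still in shock but not a failure.
- Goal *and*, failure *or*: no conflict.

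Only the last reading is consistent, and it departs from the plain *or* printed under Rescue therapy.

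**Step 3. Recovery time.** Entry admits three states. In one of them (urine output alone), MAP is not low at the start, so the time to restore it is zero or undefined.

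**Step 4. Boundaries.** MAP of exactly 50 is neither shock (<50) nor goal (>50). Urine output of exactly 1 meets the intervention goal (≥1) but not the rescue goal (>1). These are wording points only.

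**Step 5. Size.** In an arm, the any-of failure rate minus the all-of failure rate equals the share of children who end with exactly one abnormal component. At the planned 45 per arm, each such child is worth 1/45 = 2.2 percentage points. The article gives no share. Purely as assumed values, 0, 2 or 9 such children would give gaps of 0, 2/45 = 4.4 or 9/45 = 20.0 points. A between-arm difference moves only by the difference in shares, and by nothing if the shares are equal.

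**The case against.** The strongest reply is that entry and goal should be read as a pair, so that the goal is to reverse whatever put the child in shock. That is a sensible reading and may be what was intended, but the article does not say so. It also leaves open the child who enters with both components low and corrects one, whom the plain *or* under Rescue therapy would call at goal.

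On the failure list, any-of is the natural reading. The heart failure list that follows is labelled as a combination of findings and the failure list is not; the lost layout also says nothing about a connector. This stands, and it weakens any claim that the two readings deserve equal weight. It does not remove the conflict, because under any-of a child at goal by the printed *or* is still a failure.

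On recovery time, an analysis plan or the full protocol may restrict who enters the analysis. The article, however, states the definition itself, and that definition fails for a child its own entry rule admits.

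A reader might infer that hypotensive children would be left without treatment. The documents do not support that: "If the child becomes hypotensive again, we reintroduce the previous dose and follow the same procedure for further iteration"; hydrocortisone is added "For those patients whose MAP is not restored with inotropes"; and in rescue, "for doses and selection of any inotrope(s), we are following the recommendation from the Paediatric intensive care unit (PICU) consultant". A reader might also infer widespread misclassification from the number of conflicting states. Logical states are not children, and their frequency is not given.

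**Conclusion.** The point holds for the definitions as printed. A child with exactly one abnormal component can be in shock, at goal and (on the natural any-of reading) a treatment failure at the same time. MAP recovery time has no useful value for a child enrolled on urine output alone.

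The reach is two secondary outcomes, together with the literal wording of the titration and rescue goals. A reader might carry this over to the main result, but neither 28-day case fatality nor the sample size is built on these rules. Nothing is claimed about the other secondary outcomes. The size of the effect cannot be computed, because the article does not report how many children enter or end with one abnormal component. The conclusion assumes only that the *or* branch of the entry rule is used as printed.

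**What to change.** **Outcome classification.** Define treatment failure as MAP<50 or urine output <1 mL/kg/hour at the end of the intervention. Keep the separate failure route for blood not arranged within 1 hour. Apart from that route, define success as the exact complement: MAP≥50 and urine output ≥1. Use the same inequalities in every section.

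**Goal wording.** Replace the *or* under Study intervention and procedure and under Rescue therapy, at least so that a child with MAP<50 is never at goal. Leave vasopressor escalation for isolated low urine output to the PICU consultant, who already guides rescue doses. A compulsory change to titration is not needed.

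**Recovery time.** Record which component qualified the child at enrolment, and analyse MAP recovery time only among children with MAP<50 at enrolment.

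**Cost.** An ethics-board amendment to the wording and one case-record-form item. MAP and urine output are already followed every 15 minutes during the intervention, so children already enrolled (18 as of August 2022) should be classifiable from existing records. The downsides are a smaller denominator for recovery time, and that children with persistent oliguria from kidney injury count as failures even when MAP is restored. Urine output also remains hard to measure in girls, as the article says. The amendment should name the time at which the intervention ends: the failure definition gives 2/3 hours, while Table 1 gives 1 hour for the drugs and 3 hours for blood.

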#### Mean arterial pressure

MAP is calculated from systolic blood pressure (SBP) and diastolic blood pressure (DBP) by using a formula: DBP added to one-third of pulse pressure (subtraction of the DBP from the SBP).

#### Treatment failure

Treatment failure is defined if an intervention results in

MAP<50 mm Hg.Urine output is <1 mL/kg/hour, at the end of intended intervention over 2/3 hours.

Heart failure (a combination of findings)

Age-specific tachypnoea.Tachycardia.Enlarged tender liver.Pedal oedema (new or worsening).Basal crackles.Gallop.Response to furosemide.

Signs of improvement (during first hour/second hour of fluid bolus therapy).

Pulse rate falls.Pulse volume improves.Respiratory rate falls.No signs of pulmonary oedema.

Signs of deterioration (during first hour/second hour of fluid bolus therapy).

Breathing rate increases by 5/min.Pulse rate increases by 15/min.Liver enlarges (by measuring size at the beginning of fluid resuscitation and at the time of deterioration).Fine crackles at the lung base or throughout the lung fields.Oedema (new or worsening).Galloping heart rhythm.

#### Acute kidney injury

Acute kidney injury is defined as an increase in serum creatinine by ≥0.3 mg/dL from baseline within 48 hours or, an increase in serum creatinine to ≥1.5 times baseline or age-specific upper limit of reference interval or, urine volume ≤0.5 mL/kg/hour for 6 hours.

#### Recovery time

Time required for the restoration of MAP after starting the intervention for shock.

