Information is also collected about each child’s feeding practice, which included their history of breastfeeding, formula feedings, or alternative complementary feedings, and also immunisation status. Data on clinical examination findings are recorded by the study physician and include pulse, respiratory rate, axillary temperature, anthropometric measurements (ie, height, weight, mid-upper arm circumference (MUAC) for calculation of Z score), chest auscultation, oxygen saturation, presence or absence of chest wall indrawing, cyanosis and mental status (ie, normal, irritable or lethargic) and response (according to alert, response to voice or pain, unconscious (AVPU) scale). Each child’s weight is measured by using an electronic weighing scale with a precision of 0.1 kg; length is measured using a standard-length board with a precision of 0.5 cm and MUAC is measured using a standard MUAC tape with a precision of 0.2 cm by the trained and experienced study nurse of Dhaka hospital. Fever is defined when the axillary temperature is 38°C or greater. Respiratory rate is counted for a full 60 s by exposing the trunk when the child is awake and calm; the presence of lower-chest-wall indrawing is noted at the same time. Oxygen saturation is measured using a portable pulse oximeter (Handheld Vital Signs Monitors-NT1D, Solaris Medical Technology, USA) with a probe on a finger or toe when the child breathes in room air. Oxygen saturation of <90% is defined as hypoxaemia, which is an indication for supplemental oxygen therapy by using BCPAP. Blood group and Rh typing are done at the bedside and we exclude the child having negative blood groups.

Bedside Hb (if not known) is checked by using HemoCue Hb 301 analyser (HemoCue AB, Sweden) during the screening period to exclude severely anaemic children requiring an urgent blood transfusion. The length of ICU stays, the total length of hospitalisation and time-to-achieve-recovery (time required for the restoration of mean arterial pressure (MAP) after the starting of the intervention for fluid refractory shock) are recorded. We are also keeping a record of stool and urine volume. Any deterioration or adverse events (ie, signs of heart failure or need for mechanical ventilation) are also documented. Both the study and outcome are recorded including treatment failure/success, hospital discharge, referrals and deaths or left against medical advice.

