### Laboratory testing and sample handling

We are performing laboratory tests after the enrolment of a child in the study that includes blood for haemoglobin percentage, total and differential counts of white cell count (WCC), haematocrit, blood culture and antimicrobial susceptibility of pathogens, serum electrolytes and creatinine, calcium and magnesium, serum bilirubin, serum lactate, C reactive protein, procalcitonin and cardiac troponin I, stool (rectal swab for cholera, Salmonella, Shigella and Campylobacter) and urine culture, chest radiograph, and arterial or capillary blood gas analysis. We are also doing a test for the exclusion of dengue during the dengue prevalent period in the country. We are checking serum lactate at enrolment and 4–6 hours after enrolment. Our target is to send samples for laboratory tests within 30 min to 1 hour of enrolment. When a child is in shock, very often it is difficult to get an adequate amount of blood for proposed testing. Then we prioritise tests based on clinical relevance. We are doing the blood grouping, screening and cross-matching while we are following a child for study eligibility. We are performing cardiac ultrasonography during screening, enrolment and 4–6 hours later after enrolment. As we are enrolling children 24×7, the study physicians are doing the bedside cardiac ultrasound and storing the images of specific preselected parameters. Later the images are reviewed by experienced cardiologists to get the measurements.

We are archiving blood samples and planning to check serum leptin at the end of the study.

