## Ethics

This study has been approved by the institutional review board (IRB) of the icddr, b (Protocol No. PR#20021, version 2.2, dated 21 July 2022). We are conducting the study in compliance with the ‘Declaration of Helsinki’ (2000), Guideline for Good Clinical Practice. Before enrolment, we collect signed informed consent from the parents or caregivers of the children. We are strictly maintaining privacy, anonymity and confidentiality of data or information identifying the patients or caregivers. Participants’ medical information, particulars of treatment and laboratory test results will be kept confidential and under lock and key; only the research staff will have access to this information. The risk to enrolled subjects from participation in the study is minimal. Adverse medical events are anticipated as the study is enrolling critically ill patients. This protocol has been reviewed and approved by the DSMB of icddr, b. DSMB is a five-membered board that independently reviews the activity of the study. We are reporting the occurrence of any serious adverse event (eg, death) to the DSMB within 24 hours of the event and will follow their recommendations. There is no influence of the funder at any stage of the research, starting from study design and up to publication. Study patients are recruited into three different groups. For this clinical trial, injection epinephrine and injection dopamine are being used in fluid refractory shock. These drugs are already in use in the ICU of Dhaka hospital of icddr, b.^22^ WHO recommends blood transfusion, and we are routinely practising it. Regardless of the study result, finally, it will be disseminated.

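### Recovery time is counted from the start of treatment rather than from randomisation, which drops the wait for blood and shortens the blood arm's recorded times

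*Protocol article*

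**What the plan says.** Recovery time is defined twice in the protocol article, with the same start. Under Operational definition it is "Time required for the restoration of MAP after starting the intervention for shock". Under Collection of baseline information it is recorded as the "time required for the restoration of mean arterial pressure (MAP) after the starting of the intervention for fluid refractory shock". Outcome measures lists time to recovery among the secondary outcomes.

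Study intervention and procedure foresees a wait in the blood arm. Maintenance fluid is given "during the arrangement of blood transfusion and intervention with inotropes", and a time limit is set: "If blood could not be arranged within 1 hour after the event of fluid refractory shock, we will start rescue therapy", with the event counted as treatment failure. No comparable wait is described for dopamine or epinephrine. Laboratory testing and sample handling describes preparation before allocation: "We are doing the blood grouping, screening and cross-matching while we are following a child for study eligibility".

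On deaths, Reporting of adverse events states: "Serious adverse events (deaths) after initiation of the study intervention are recorded and presented to the DSMB within 24 hours of the event". The Ethics section states: "We are reporting the occurrence of any serious adverse event (eg, death) to the DSMB within 24 hours of the event", and names no start point.

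**The concern.** A time-to-event comparison respects the randomisation only if the clock starts at the same moment in every arm, at or before the point where the arms diverge. Here it starts after allocation, at a moment that depends on the arm. Time spent waiting for blood belongs to the blood strategy: the Background section itself names the difficulty of getting safe blood quickly as a drawback of that strategy. The definition removes that time from the one outcome that measures speed of recovery.

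Some children also have no start time. If blood does not come and rescue begins, the allocated treatment never started, so recovery time is either undefined or starts at rescue with the wait erased. If MAP recovers on maintenance fluid before transfusion, recovery precedes the start of the clock. If the child dies waiting, the clock never starts. Losing such children, who would be mainly in one arm, conflicts with the intention-to-treat analysis promised under Data collection, management and analysis.

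**Working it through.** **1. Start points side by side.**
- Case fatality: 28±3 days from the day of enrolment (Outcome measures).
- MAP stabilisation: 48 hours after enrolment (Outcome measures).
- Recovery time: start of the intervention (the two definitions above).
- Table 1: Hour 0 for enrolment and allocation, and study treatment also from Hour 0 in all arms, with no wait shown.

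Recovery time is thus the exception among the plan's own timed outcomes.

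**2. Direction of the error.** Let w be the time from randomisation to the start of treatment. Then recorded time = (time from randomisation to recovery) − w. Since w cannot be negative, recorded time can only be too short. If recovery truly takes 2 hours from randomisation (illustrative), a blood-arm child with w = 0.25, 0.5 or 1 hour is recorded at 1.75, 1.5 or 1 hour.

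**3. Bound on w.** The hour runs from the shock event. Taking arrangement of blood as the start of transfusion, w ≤ 1 hour − (time from shock event to randomisation). Consent and randomisation follow the diagnosis of refractory shock, so the subtracted term is positive. If it were 15 minutes (assumed), w could be at most 45 minutes. Cross-matching during screening shortens w further. The article gives no observed waits.

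**4. The plan's sample size.** For 61% versus 31%, two-sided 0.05, 80% power, unpooled variance: n = (1.960 + 0.842)² × (0.61×0.39 + 0.31×0.69) / 0.30² = 39.4, so 40 per arm. With 10% dropout, 40/0.9 = 44.4, so 45 per arm and 135 in total. This reproduces the plan and does not depend on the present point. It supplies only the 45 used next.

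**5. Effect on the test (illustration).** Assume two arms truly equal when timed from randomisation, 45 per arm, normal times, a mean wait w omitted from the blood arm and none from the other. The SD is assumed, because the article gives none. The chance of a significant result favouring blood is Φ( w / (SD × √(2/45)) − 1.96 ), with √(2/45) = 0.2108. For w = 0.5 and SD = 1: 0.5/0.2108 − 1.96 = 0.41, giving 66%.

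| SD (h) | w = 0.25 h | w = 0.5 h | w = 1 h |
|---|---|---|---|
| 1 | 22% | 66% | 99.7% |
| 2 | 9% | 22% | 66% |
| 4 | 5% | 9% | 22% |
| 8 | 3.5% | 5% | 9% |

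The nominal rate in that direction is 2.5%. The last column is the extreme case and, by step 3, is not expected as a mean.

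**6. Deaths in the wait.** If 0.5% to 5% of 45 blood-arm children died before transfusion (assumed), that is 0.225 to 2.25 deaths. Read literally, the adverse-event section would not cover them. The Ethics section would, and the primary outcome counts them in any case.

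**The case against.** The strongest reply is that the effect is small and confined to one secondary outcome. Blood is prepared during screening, a volunteer donor list and two dedicated technologists are in place, and part of the allowed hour has passed by the time a child is randomised. The drugs also have to be made up as infusions, so their wait need not be zero. All of this limits the size, and the documents cannot show what difference in waits remains. It does not change the direction as long as blood takes longer to start than a pump infusion, which is what the plan's provision for the wait implies.

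It can also be said that timing from first treatment answers a fair question about how fast each treatment works. It does, but as a description: the groups compared are then children who reached treatment, not the groups as randomised.

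A third reply is that coding of deaths and rescues belongs in an analysis plan that is not shown. That holds for the choice of method. The start of the clock, however, is fixed in the article, twice.

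A reader might go further and infer that whatever happens during the wait is lost to the trial. That is not so. Case fatality runs from enrolment and is analysed by intention to treat, MAP stabilisation is also timed from enrolment, and blood that cannot be arranged in time is counted as treatment failure. A reader might also infer that the DSMB receives an incomplete count of blood-arm deaths. The documents do not establish this, because the Ethics section reports any serious adverse event without a start point.

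**Conclusion.** The point holds for time to recovery. Its definition starts the clock after randomisation at an arm-dependent moment, shortens the blood arm's recorded time by an unknown amount, and leaves some children without a start time. The omitted wait is at most 1 hour per child and probably less; a full hour should not be read as the expected bias. Whether the test is materially distorted depends on the mean wait and the SD, neither of which is given: on the assumptions shown, the distortion ranges from slight (SD 8 hours, short wait) to serious (SD 1 hour, half-hour wait). It rests on the inference that the drug arms start sooner than blood, which the article implies but does not state.

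The primary analysis, the sample size, MAP stabilisation and treatment failure stand as they are. On deaths, what remains is an inconsistency between two sections. The change should be made, but it is not a flaw in the main design.

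**What to change.** - Define recovery time from randomisation in all three arms, in both the operational definition and the data-collection section.
- Record the clock time of randomisation for each child. Hour 0 in Table 1 is a schedule label, and the article describes no such time stamp. For children already enrolled (18 by August 2022), recover it from trial records or, failing that, use the time of enrolment in every arm alike.
- Keep children who recover, die or go to rescue before transfusion in the analysis from that same start. The exact handling of death and rescue can be set in the analysis plan.
- If speed after the start of treatment is still of interest, report it descriptively, together with the time from randomisation to treatment by arm.
- Reconcile the adverse-event and Ethics sections so that both cover deaths from randomisation.

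The cost is a few wording changes and one recorded time. Sample size, treatments and primary analysis do not change.
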